## Abstract

**Introduction:**

Congenital heart disease (CHD) represents the most common birth defect, affecting from 0.4% to 1.2% of children born in developed countries. The survival of these patients has increased significantly, but CHD remains one of the major causes of neonatal and childhood death. The aetiology of CHD is complex, with some evidence of both genetic and environmental causes. However, there is still lack of knowledge regarding modifiable risk factors and molecular and genetic mechanisms underlying the development of CHD. This study aims to develop a prospective cohort of patients undergoing cardiac procedures that will bring together routinely collected clinical data and biological samples from patients and their biological mothers, in order to investigate risk factors and predictors of postoperative-outcomes, as well as better understanding the effect of the surgical intervention on the early and long-term outcomes.

**Methods and analysis:**

Children OMACp (OMACp, outcome monitoring after cardiac procedure in congenital heart disease) is a multicentre, prospective cohort study recruiting children with CHD undergoing a cardiac procedure. The study aims to recruit 3000 participants over 5 years (2019–2024) across multiple UK sites. Routine clinical data will be collected, as well as participant questionnaires collecting sociodemographic, NHS resource use and quality of life data. Biological samples (blood, urine and surgical waste tissue from patients, and blood and urine samples from biological mothers) will be collected where consent has been obtained. Follow-up outcome and questionnaire data will be collected for 5 years.

**Ethics and dissemination:**

The study was approved by the London–Brent Research Ethics Committee on 30 July 2019 (19/SW/0113). Participants (or their parent/guardian if under 16 years of age) must provide informed consent prior to being recruited into the study. Mothers who wish to take part must also provide informed consent prior to being recruited. The study is sponsored by University Hospitals Bristol and Weston Foundation Trust and is managed by the University of Bristol. Children OMACp is adopted onto the National Institute for Health Research Clinical Research Network portfolio. Findings will be disseminated through peer-reviewed publications, presentation at conference, meetings and through patient organisations and newsletters.

**Trial registration number:**

ISRCTN17650644.

Strengths and limitations of this studyLarge multicentre, prospective cohort study collecting clinical/questionnaire data and biosamples from children with congenital heart disease (CHD) undergoing cardiac procedure and their biological mothers.Combined data and samples analyses will allow identification of risk factors and short-term, medium-term and long-term outcome predictors.Cost-effective method of generating a persistent data and sample registry accessible both nationally and internationally.The cohort does not include control data from healthy subjects; however, this will be obtained from external sources and record linkage.Only patients requiring a cardiac procedure are included, not representing all CHDs.

## Introduction

Congenital heart disease (CHD) represents the most common birth defect, affecting from 0.4% to 1.2% of live-born children in the developed countries,^1 2^ and remains one of the major causes of neonatal, infant and childhood death.^2 3^ CHD is generally defined as a gross structural abnormality of the heart or intrathoracic great vessels present at birth that is actually or potentially of functional significance.^4^

The aetiology of CHD is complex, with some evidence of both genetic and environmental causes. However, there is still a lack of knowledge regarding modifiable causal risk factors.^5^ Furthermore, the molecular and genetic mechanisms underlying the development of CHD have not been clearly elucidated and the identification of specific subphenotypes of CHD remains challenging.^6 7^

While the incidence of CHD has remained unchanged, the survival of these neonates and infants has increased dramatically in the last two decades,^8^ leading to a rise in the numbers of adults with CHD. For example, in 2000, there were nearly equal numbers of adults and children with severe CHD,^9^ highlighting the need to better understand CHD aetiology, including modifiable risk factors and molecular genetic mechanisms, so that methods of preventing CHD can be developed to reduce its disease burden.^10^

Current research on potentially modifiable maternal risk factors suggests that maternal smoking, greater adiposity and associated dyslipidaemia, gestational diabetes and hypertensive disorders of pregnancy are associated with increased incidence of CHD.^11–13^ However, most of these studies have been cross-sectional or case control, with relatively small number of cases or have not adjusted for key confounders and therefore cannot determine degree of causality. Genome-wide association studies (GWAS) of the fetal/child genome including up to 2000 cases have identified some robust genetic variants associated with all or specific CHDs, but lack power to identify modest genetic associations, particularly with subtypes of CHD.^14^ GWAS of maternal genotype are rare and few aetiological studies have used methods to try and unpick causal effects from association, such as using genetic variants as instrumental variables in Mendelian randomisation studies, negative control studies or within sibship analyses.^15^ It is necessary to apply best methods to establish the most relevant targets for interventions in order to facilitate future randomised controlled trials assessing causality.

Patients with CHD often require multiple complex surgeries and life-long medical therapies and follow-up. These therapies are ineffective in up to 50% of the treated patients and involve significant morbidity, long-term mortality and substantial cost.^16^

The development of predictive tools and integrated information for advancing CHD clinical diagnosis and prognosis is one of the most prominent challenges of clinical cardiology. Traditional research methods have largely failed to advance an understanding of early complications and longer-term failure of cardiac surgery interventions. However, application of large-scale genomic^17^ and metabolomic^18 19^ approaches to the prediction of complications and applied epidemiological techniques to investigate causality^20 21^ have the potential to advance mechanistic understanding and streamline therapeutic development.^22^

In parallel, Electronic Health Records data generated and collected during normal clinical care are increasingly being linked and used for translational cardiovascular research.

Our ability to advance medical care and efficiently translate science into modern medicine is bounded by our capacity to access and process these ‘Big Data’. From human genetics and ‘omics’ to routine clinical documentation and from internal imaging to motion capture, the volume and variety of ‘Big Data’ is bound to change in medicine. Statistical, mathematical, visualisation and computational approaches, from a wide range of disciplines, as well as systems for innovative interventions, are needed to keep apace of the complexity in disease prediction and prognostics and to advance medicine.

The study aims to develop a prospective cohort of patients undergoing surgery and/or catheterisation that will bring together routinely collected clinical data as well as biological samples from both patients and their biological mothers, in order to investigate further risk factors of CHD and predictors of postoperative outcomes. Our ambition is to make this a persistent resource accessible to high-quality future CHD studies, nationally and internationally. Outcomes and the corresponding data and biomarkers to be examined will be directed by the hypothesis of substudies and/or external ethically approved studies accessing the registry.

## Methods and analysis

### Study design

Children OMACp (OMACp, outcome monitoring after cardiac procedure in congenital heart disease) is a multicentre, prospective cohort study recruiting patients diagnosed with CHD and undergoing a cardiac procedure (catheterisation and/or surgery) and their biological mothers. The study aims to evaluate short-term, medium-term and long-term health outcomes and collect biological samples for patients undergoing cardiac surgery and/or catheterisation for CHD. Biological samples and risk factors information will also be collected from patients’ biological mothers where consent has been obtained.

### Study setting

The cohort will recruit patients attending Bristol Royal Hospital for Children, and up to 11 additional hospitals. At the time of writing, the study is recruiting at Bristol Royal Hospital for Children, Leicester Royal Infirmary and Dublin Children’s Hospital.

The planned duration of the study is 10 years (5 years recruitment period and 5 years for follow-up).

### Research questions

Specific research questions and objectives include, but are not limited to:

To identify the maternal genetic and potentially modifiable risk factors for CHD.To identify clinical, genetic and environmental factors that act as predictors for short-term, medium-term and long-term clinical outcomes.To determine the effect of clinical management strategies on outcomes of CHD including perioperative and operative care.To identify factors that influence National Health Service (NHS) resource use for patients with CHD.To evaluate the impact of CHD on neurological development and school performance.To evaluate the impact of CHD surgical correction on organ function (such as heart, liver, kidney that are potentially damaged during the operation).To explore the potential of deep phenotyping extreme high-risk groups including those with single ventricle and cyanotic heart disease.To identify the impact of CHD on sleep disorders.To evaluate the accuracy and prediction of imaging cardiac data with early and long-term complications.To use machine learning platforms for developing personalised treatment for CHD (eg, pharmacogenetics and epigenetics).

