#### Inclusion criteria

Patients must:

be aged between 0 months and 18 years of age.diagnosed with CHD.undergoing cardiac surgery and/or catheterisation.

The person giving consent must:

have capacity to consent (if participant 16–18 years of age) or assent (if participant age 11–15).have capacity to consent and parental responsibility for the participant (if participant under 16 years of age).

Mothers must:

have a biological child enrolled in Children OMACp.have capacity to consent.

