#### Exclusion criteria

The study will exclude patients and biological mothers who are unable to give informed consent and/or assent, those with a main residence outside of the UK and Ireland and those under the care of Social Services.

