### Analysis

The study will provide a resource for several research questions to be addressed (see above). There are two broad types of analyses that the cohort will be used for: (a) analyses that addresses questions requiring data from patients with CHD only and (b) analyses addressing questions that require a healthy control/comparison group.

A key focus initially will be on prediction and risk stratification, in particular developing accurate tools for predicting those children who are at most risk of adverse outcomes after surgery, and who are therefore likely to benefit from tailored care-packages and more intense monitoring post-surgery.

Sociodemographic, clinical and ‘omics’ (eg, genomics, proteomics, epigenomics and metabolomics) data will be considered for inclusion in the prediction models. Machine learning approaches, that allow for a large number of potential predictors to be studied simultaneously, while accounting for their correlation structure and potential interactions to be taken into account, will be used to identify a ‘top-set’ of potential prediction models. We will then consider those models further with respect to discrimination, calibration and clinical utility, selecting those that maximise cost-effectiveness. We will use internal validation procedures but also (with extension of the network beyond Bristol) have the ability to externally validate the prediction tool in cohorts from outside of Bristol.

With addition of maternal data to the study, we will also explore causal maternal risk factors using multivariable regression analyses. We will also contribute data and academic input to GWAS consortia to identify both fetal and maternal genetic variants associated with CHD and use those in two-sample Mendelian randomization.

When reporting outcomes, participants will be grouped according to the type of operation and type of CHD. The Children OMACp cohort allows for the collection of routine clinical operative and perioperative data alongside short (eg, acute kidney injury) and long-term (eg, mortality) clinical outcomes. We will use data and biosamples to answer hypothesis-driven research questions such as assessing the effect of cardiopulmonary bypass duration on renal injury. Analyses will be appropriately powered assessing subgroups of the overall cohort for individual research questions.

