## Discussion

Here we present the Children OMACp study, a unique resource facilitating research into CHD by enabling efficient collection of large amounts of data from medical records and questionnaires, as well as biological samples from multiple hospitals performing heart procedures on this specific cohort of patients and their biological mothers.

OMACp has many strengths, providing the ability to develop a cohort of patients with CHD in UK and Ireland, for robust hypothesis-driven research and will focus initially on identification of risk factors and outcome predictors for short-term, medium-term and long-term outcomes, offering the basis to explore risk, prognosis, outcome and management. The final goal is to create a cost-effective, persistent, data and biosample repository that can be made available to other high-quality ethically approved studies to support future CHD research nationally and internationally.

Combining perioperative data, maternal risk factors information and biosamples, the study will explore the potential for machine learning and personalised medicine, by utilising artificial intelligence models to review sociodemographic, clinical (including imaging data) and multiple ‘omics (eg, genomic, epigenomic, proteomics and metabolomics) to better risk stratified the extreme large heterogeneous diagnosis of CHD and their surgical early-term and long-term outcomes and prepare individually tailored approaches to care. The collection of maternal data will contribute information on the potential causality of maternal risk factors.

While initially, the study will collect only minimal information on father’s history (via the mother’s questionnaire), in future, the aim is to extend the recruitment to fathers to assess impact of father’s genetics, medical and lifestyle factors on children CHD risk and outcomes. Furthermore, there will be potential for including additional non-cardiac malformations.

Although only patients requiring a cardiac procedure are included, representing a fraction of all CHDs, this is the group that will most greatly benefit from any advances in the management and tailoring of medical care.

In addition, while the cohort does not include healthy subjects, the study has access to use data and samples from external sources (eg, ALSPAC and record linkage) as healthy controls, when necessary.

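### Objective 1 and the maternal causal analyses are worded as being about CHD, but the cases are only live-born children who survived to, and needed, a procedure; this can bias the estimates, not only limit representativeness

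*Protocol article*

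**What the plan says.** The Research questions section of the protocol article opens with the objective "To identify the maternal genetic and potentially modifiable risk factors for CHD". The Analysis section adds that "we will also explore causal maternal risk factors using multivariable regression analyses", and on the genetic side: "We will also contribute data and academic input to GWAS consortia to identify both fetal and maternal genetic variants associated with CHD", with the resulting variants then used in two-sample Mendelian randomisation. The same section looks to outside sources such as ALSPAC and data linkage for healthy controls. The Discussion states: "The collection of maternal data will contribute information on the potential causality of maternal risk factors".

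Under Inclusion criteria, a patient must be aged 0 to 18 years, have a CHD diagnosis and be "undergoing cardiac surgery and/or catheterisation". A mother must "have a biological child enrolled in Children OMACp".

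The strengths and limitations list says: "Only patients requiring a cardiac procedure are included, not representing all CHDs". The Discussion repeats that these patients are a fraction of all CHD, and defends the restriction because this group stands to gain most from better management.

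**The concern.** The objective asks what causes CHD. The recruited cases answer a narrower question: which maternal factors are found more or less often among mothers whose affected child was born alive, lived until a procedure and needed one. An affected pregnancy that ended in termination or fetal death, a child who died before any procedure, and a child whose defect needed none cannot contribute a case.

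For the prognostic objectives this only defines the population. For an aetiological comparison with healthy controls it can bias the estimate. A factor that has no effect on the heart but changes, for example, survival to a procedure in affected children would be associated with case status. A factor that does cause CHD could have its effect hidden. The Introduction faults earlier studies for being unable to settle causality and wants targets for intervention, so the distinction affects what the cohort may conclude. Eligibility is applied at recruitment, so later analysis cannot recover the missing cases.

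**Working it through.** **The article gives no figure to reproduce.** It states no selection probability and no target odds ratio, so the check is a derivation followed by an illustration with assumed values.

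**Inputs from the article**
- Case entry: live child, diagnosed, undergoing a procedure (Inclusion criteria).
- Mother's entry: through an enrolled child only (Inclusion criteria).
- Controls: external and healthy, with the source still open (Analysis).
- CHD frequency: 0.4% to 1.2% of live births (Introduction).
- The Introduction names CHD as a leading cause of death in newborns, infants and children, so loss before a procedure is a real step.

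**Formula.** Let 1 and 0 denote exposed and unexposed pregnancies, N their number and p the probability of CHD. Let s be the probability that an affected pregnancy becomes an eligible case: P(live birth) × P(alive until procedure) × P(procedure needed). Let c be the corresponding probability that an unaffected pregnancy can supply a control.

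- Available cases: N1·p1·s1 and N0·p0·s0.
- Available controls: N1·(1−p1)·c1 and N0·(1−p0)·c0.
- Observed OR = true OR × (s1/s0) / (c1/c0).

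The CHD frequency drops out, so the result is the same at 0.4% and 1.2%.

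**When there is no bias.** If s1 = s0 and c1 = c0, the multiplier is 1. If a factor changes live birth by the same ratio in both groups, for example s1/s0 = c1/c0 = 0.80, the multiplier is 0.80/0.80 = 1. Termination after a cardiac diagnosis, death from CHD and need for a procedure are specific to cases and do not cancel in this way.

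**Illustration (all s assumed; controls unselected, c1/c0 = 1)**

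| s1 / s0 | Ratio | True OR 1.0 observed as | True OR 1.3 observed as |
|---|---|---|---|
| 0.60 / 0.80 | 0.75 | 0.75 | 0.975 |
| 0.75 / 0.80 | 0.94 | 0.94 | 1.22 |
| 0.80 / 0.80 | 1.00 | 1.00 | 1.30 |
| 0.80 / 0.60 | 1.33 | 1.33 | 1.73 |

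**Effect of cohort size.** Assume a factor with no true effect, 20% exposure among controls, equal numbers of cases and controls, and a two-sided 5% test. An observed OR of 0.80 corresponds to an exposure odds of 0.25 × 0.80 = 0.20 in cases, a proportion of 0.167. An OR of 1.20 gives odds of 0.30, a proportion of 0.231. The chance of declaring significance is:

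| Cases | Observed OR 0.80 | Observed OR 1.20 |
|---|---|---|
| 1000 | 49% | 39% |
| 1500 | 66% | 54% |
| 3000 | 92% | 83% |

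Reaching the target of 3000 therefore gives no protection. A larger cohort makes a biased estimate look more certain.

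**Why adjustment is not enough.** Multivariable regression addresses confounders that are measured and entered. The multiplier above arises from the exposure's own effect on whether an affected pregnancy becomes a case, and adjusting for other covariates does not by itself remove that.

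**The case against.** The strongest reply has four parts.

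1. **The procedure restriction is disclosed twice.** That is true, and a reader is not misled about who is enrolled. But the disclosure speaks of representativeness and is defended by benefit to management, which does not answer an aetiological objective. Losses before a procedure are not mentioned.

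2. **The Introduction defines CHD as present at birth and counts it among live births.** This weakens the part about pregnancies that ended before birth, which lie largely outside that outcome. Yet a factor that changes termination would alter CHD frequency at birth without causing the defect. Death before a procedure and CHD needing no procedure remain mismatched even on the article's definition.

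3. **The causal wording is cautious.** The article speaks of exploring causal factors and of potential causality, and prediction is its initial focus. A reader might infer that the study commits itself to a firm causal conclusion about the wrong outcome; the text does not go that far. The point concerns how the objective and the limitation are worded.

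4. **Control eligibility and sensitivity analyses may be set out in the full protocol, an analysis plan or substudy plans.** Their absence from the article is not held against it here. They appear below only as what the reworded claim needs.

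A reader might also infer that any maternal factor affecting these steps must appear as a cause or a protector. It need not: a factor acting by the same ratio in the control source cancels.

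**Conclusion.** The concern holds in limited form. The article words an aetiological objective as being about CHD, while its cases are live-born children who reached a procedure, and it treats the difference as a matter of representativeness only. Bias arises where a maternal factor changes the steps to a procedure differently in affected pregnancies than in the control source.

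Neither the size nor the direction for any exposure follows from the documents. The range 0.75 to 1.33 for a true odds ratio of 1.0 rests wholly on assumed selection probabilities and unselected controls. A mild assumed imbalance (0.75 against 0.80) moves a true 1.3 only to 1.22.

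It might be inferred that the genome-wide association and Mendelian randomisation results carry the same bias. The article does not support that: the extent of this selection there depends on the consortium case definitions, which are not given.

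**What to change.** - Restate objective 1, and the maternal analyses in the Analysis section and Discussion, as factors associated with live-born CHD that reaches catheterisation or surgery.
- In the strengths and limitations list and the Discussion, say that selection through pregnancy loss or termination, death before a procedure and need for a procedure can bias aetiological estimates, and is not only a limit on representativeness.
- Draw controls from live births where possible, and note that this removes only selection shared with controls. It cannot undo selection specific to cases.
- Accompany each causal maternal estimate with a sensitivity calculation over a stated range of (s1/s0)/(c1/c0), dividing the observed odds ratio by each value.
- For the consortium and Mendelian randomisation route, state only that the extent of this selection depends on the consortium case definitions.

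The cost is a narrower claim, some rewording and one short calculation per exposure. Recruitment and patient care do not change.
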